### 11.4 PRODUCTION, PACKAGING AND LABELLING OF IP

Production and packaging of the IP (verum and placebo), will be taken over by the sponsor, Enzymatica AB. Labelling will be provided by the sponsor (via an independent pharmacist).

The labels will contain the following information (in German), with storage information

only applicable to storage at the subjects's home:

- Randomization code
- Sponsor: Enzymatica AB, [name]
- CRO: analyze & realize GmbH, [name], [contact]
- Name of the investigational product: CMS008618 or placebo
- Batch number:
- Dosage: after symptom start, 2 sprays (1 dose) every second hour up to 6 times per day, on each day after symptom start and for 2 days after symptom stop, but not longer than 10 days in total
- Content per package:
- Study code: 008618
- "For clinical study use only"
- Store:
  - Before first use in a refrigerator
  - After first use at room temperature
- If kept cold until first use, to start use latest by: July 2019
- After first use, must not be used for longer than 10 days
- Keep out of reach of children

#### 11.5 STORAGE, INVENTORY, RETURN, TRACEABILITY AND DOCUMENTATION OF THE INVESTIGATIONAL PRODUCT

The investigational product will be provided to the CRO and/or the investigational sites by the sponsor. The CRO and/or the investigational sites will be responsible for storing the investigational product in a proper place, at the appropriate conditions and inaccessible to unauthorized persons.

The IP should be kept frozen ( $\leq -18^{\circ}\text{C}$ ) and cooled transport used for any shipments required until the time point of handing it out to the subjects.

As applicable, the CRO will distribute the investigational product to the investigator who will hand it out to the subjects (alternatively the IP may be shipped directly from the sponsor to the site(s)). The investigator (or designee) will only dispense IP to subjects randomised in this clinical investigation and record the issue and return of the IP.

The IP should be dispensed in a frozen state and the subjects should be provided material and instructions for cooled transport of the IP from the site to their home. They will also be provided with written instructions on handling, storage and use of the IP.

The subjects should store the IP:

- Before first use in a refrigerator
- After first use at room temperature. Subjects will be instructed that they should not keep the IP in a place warmer than room temperature and not carry the IP in a pocket of a clothing that may be expected to reach a temperature close to body temperature (e.g. trousers, skirt).

The empty and unused (if any) portion of the IP will be collected from the subjects at the sites and sent to the CRO for the IP accountability (per vial weight). After comple-

tion of the investigation, the unused IP will either be returned to the sponsor or destroyed (as per agreement with the sponsor).

Traceability will be ensured by use of specific batch numbers.

## 11.6 METHODS OF RANDOMISATION AND BLINDING

The clinical investigation will be conducted in a double-blind randomised manner (block randomisation). The subjects will be randomised at the screening visit. The randomisation list will be provided to the sponsor's assigned responsible person (not involved in the study) by the statistician responsible for generation of the randomisation list. The ratio of randomisation between the verum and placebo will be 1:1. Random numbers will be assigned to the subjects in a sequential order based on time of randomisation at each investigational site (several whole blocks will be allocated to each centre). Randomisation list will be concealed to the investigational sites. It will be stored under lock and key by the sponsor until database closure. After database closure and sign-off of the statistical analysis plan, the sponsor's responsible person will provide the randomisation list to the statistician responsible for the statistical analysis (and the project manager at the CRO, as appropriate).

## 11.7 BLINDING AND EMERGENCY ENVELOPES

Verum and placebo are identical in appearance, as well as packaging and labelling, so that study participants, CRO and investigators are blinded to treatment assignment. The independent statistician will generate the emergency envelopes for all subjects that will be provided to the CRO and from the CRO to the investigators to be stored in the Investigator Site File (ISF). All emergency envelopes will be collected during close-out of the investigational site at the end of the study.

## 11.8 UNBLINDING AND PROCEDURES FOR BREAKING CODES

The emergency envelope should be opened by the investigator only in emergency cases (e.g. serious adverse event), in which the investigator suspects a causal relation with the investigational product, requiring unblinding for the decision of the immediate medically required treatment. In case of an emergency unblinding, the investigator will contact the CRO within 24 hours (latest within the very next working day). The CRO will promptly inform the sponsor. Opening of an emergency envelope should be documented in the CRF including the opening person, specific reason for and date and time of unblinding. The same information should be documented on the opened emergency envelope and signed by the investigator. Care must be taken not to unblind any other members of the study team, including CRO and sponsor.

## 11.9 COMPLIANCE

### 11.9.1 Overall Compliance to IP use

Evaluation of IP usage will be performed during statistical evaluation at study end, based on the return and documentation of unused investigational product (per vial

weight) as compared to duration of the period defined for IP usage. A subject is classified as compliant when applying at least 80% of the correct quantity of investigational product.

### **11.9.2 Compliance at the Start of IP use**

The IP use should start when the following conditions have been fulfilled:

- answering "Yes" to either of the questions in the subject daily diary: "Do you think/feel you have a cold?" or "Do you think/feel you are coming down with a cold (might be having first signs of cold)?" AND
- Jackson score of at least 1 in the subject's cold diary (mild = present, but not disturbing or irritating) for any symptom except headache

A subject is classified as compliant when applying the IP by the morning of the next day after the first day of a defined common cold (Jackson score  $\geq 1$ , except headache).

### **11.9.3 Compliance at the Start of Filling out the Subject Cold Diary**

The subjects have to start filling out the cold diary on the first day they answer "Yes" to either of the questions in the subject daily diary: "Do you think/feel you have a cold?" or "Do you think/feel you are coming down with a cold (might be having first signs of cold)?".

A subject is classified as compliant when starting records in the cold diary by the morning of the next day after they answer "Yes" to the above questions in the evening.

## 12 CONCOMITANT TREATMENT

The subjects report use of any concomitant treatment (e.g. other medical devices, medication, any natural health products including food supplements etc.) to the investigator at the first visit. The investigator documents the following information in the CRFs: substance, dosage, start and duration, reason. Subjects will also be advised to inform the investigators of any treatment performed throughout the clinical investigation period.

During the study, the following concomitant treatment listed in the exclusion criteria should not be used:

- products that may influence the study outcome (e.g. immune suppressants/immune stimulants including natural health products, analgesics/anti-rheumatics, anti-phlogistics, anti-tussives/expectorants, mouth or throat therapeutics, decongestants, antibiotics, anti-histaminergic drugs, nasal drops/spray), except for the defined “rescue” treatment
- influenza vaccination.

The following treatment is defined as “rescue” medication during the period of common cold/ start of IP use until V3:

- paracetamol (max. 2 g/day),
- ibuprofen (max. 400 mg/day),
- saline nose drops or nose spray
- as well as antibiotics (in case they are medically required for another ailment following the confirmation of the bacterial infection, however not to be used for common cold).

At enrollment, the investigator informs the subjects that any concomitant treatment that could possibly influence the outcome of the study is not allowed, except for the defined rescue medication.

## **13 CONDUCT OF THE CLINICAL INVESTIGATION**

### **13.1 VISIT 1 (V1, SCREENING, RANDOMISATION) – ALL SUBJECTS**

- Oral and written information about the nature, purpose, possible risks and benefits of the study provided to the subjects by the investigator
- Written consent of the subject to participate; the subject understands the requirements of the clinical investigation and is willing to comply
- Questioning and documentation of the medical history, concurrent diseases and concomitant treatment, demographic and anthropometric data, and physical examination by the investigator
- Verification that the inclusion criteria are met and that there are no violations of the exclusion criteria
- Measurement of blood pressure and pulse rate
- Urinalysis
- Pregnancy test for women with childbearing potential (in urine)
- Issue of subject diary and instructions for record keeping
- Randomisation
- Issuance of IP and instruction for use
- Questioning and documentation of possible occurrence of adverse events (AEs)

Between V1 and V2, the study site will have monthly phone contact with the subjects as a reminder about the study.

### **13.2 VISITS FOR SUBJECTS WITH SYMPTOMS**

#### **13.2.1 Visit 2 (V2), within 1– 3 Days After Symptom Start**

- Questioning and documentation of possible occurrence of AEs/device deficiencies
- Questioning and documentation of new or changed concomitant treatment
- Control and re-issue of the subject diary
- Checking criteria for further participation
- Physical examination
- Measurement of blood pressure and pulse rate
- Assessment and documentation of any present symptoms (cold confirmed or another disorder diagnosed)

#### **13.2.2 Visit 3 (V3, Final), 16 ± 4 Days After Symptom Start**

- Questioning and documentation of possible occurrence of AEs/device deficiencies

cies

- Questioning and documentation of new or changed concomitant treatment
- Return and control of the subject diary
- Return of IP and accountability
- Physical examination
- Measurement of blood pressure and pulse rate
- Global evaluation of efficacy by subjects and investigators (4-point categorical scale)
- Global evaluation of tolerability by subjects and investigators (4-point categorical scale)

### 13.3 VISIT FOR SUBJECTS WITHOUT SYMPTOMS DURING THE STUDY PERIOD: TERMINATION VISIT (TV), 16 WEEKS $\pm$ 7 DAYS AFTER V1

- Questioning and documentation of possible occurrence of AEs
- Questioning and documentation of new or changed concomitant treatment
- Return of the subject diary
- Return of IP

### 13.4 DEMOGRAPHIC AND ANTHROPOMETRIC DATA

The subject's age (years), gender (male/female) and ethnicity will be assessed and documented in the CRF at V1.

### 13.5 MEDICAL HISTORY / PHYSICAL EXAMINATION

At V1, the subject will be questioned by the investigator regarding the medical history and will undergo a physical examination. Known pre- or co-morbidities (including the number of self-reported common colds during the past 12 months) as well as any abnormal and/or pathological findings of the examination will be systematically recorded.

A dipstick urinalysis for the assessment of glucose and proteins will be performed for all subjects and a pregnancy test in urine for women with childbearing potential.

### 13.6 ASSESSMENT OF EFFICACY

#### 13.6.1 Subject Diary

In the daily subject diary, from V1 on, the subject will be asked to answer the questions "Do you think/feel you have a cold?" or "Do you think/feel you are coming down with a cold (might be having first signs of cold)?" (in the morning and in the evening).

From the first day he/she answers „Yes“ to either of the above questions, he/she will have to start filling out the cold diary instead, to:

- record the symptoms on the Jackson scale (twice daily, in the morning and in the evening)
- record the symptoms on the Sore Throat Scale (once daily, in the evening)
- fill out the Wisconsin Upper Respiratory Symptom Survey (WURSS-21) Quality of Life section (once daily, in the evening)
- answer the question "Do you think that you are still sick with this respiratory infection?" (once daily, in the evening)
- record the use of IP (once daily, in the evening)
- record the use of any concomitant treatment / remedies, specifying the time point of use
- if he/she stayed sick at home (away from work, school etc.) due to common cold.

The cold diary should be filled out until 2 days after the subject is symptom free (=answering "No" to the question "Do you think that you are still sick with this respiratory infection?" for 2 days in a row), but not longer than 10 days in total.

If the subjects, in an exceptional case, fail to continue filling out the diary immediately when being symptom free, no data for the 2 subsequent days in the diary would be considered as having no symptoms (corresponding to answering "No" to the question "Do you think that you are still sick with this respiratory infection?").

The total composite Jackson score (Jackson et al., 1958) is calculated by summing the following 8 symptom scores: sore throat, blocked nose, runny nose, cough and sneezing (local symptoms) as well as headache, malaise, and chilliness (systemic symptoms). Local composite Jackson score is derived by summing the local symptoms and systemic composite Jackson score by summing the systemic ones. Symptoms are assessed on a 4-point scale: 0 = none (symptom not present), 1 = mild (present, but not disturbing or irritating), 2 = moderate (symptoms sometimes disturbing/irritating), 3 = severe (symptoms disturbing/irritating most of the time).

The Sore Throat is a 0-10 Likert scale where 0=not sore and 10=very sore (Russo et al., 2013; Shephard et al., 2015).

WURSS-21 (Barrett et al., 2009) is an evaluative illness-specific quality of life instrument with 21 items, designed to assess the negative impact of acute upper respiratory infection, presumed viral (the common cold). In this study, the QoL part of the WURSS-21 will be applied, from item 12 ("think clearly") to item 20 ("live your personal life").

**Wisconsin Upper Respiratory Symptom Survey – 21 --- Daily Symptom Report**

Day: \_\_\_\_\_ Date: \_\_\_\_\_ Time: \_\_\_\_\_ ID: \_\_\_\_\_

Please fill in one circle for each of the following items:

|                             | Not sick
0         | Very mildly
1      | Mildly
2           | Mildly
3           | Moderately
4       | Moderately
5       | Severely
6         | Severely
7         |
|-----------------------------|-----------------------|-----------------------|-----------------------|-----------------------|-----------------------|-----------------------|-----------------------|-----------------------|
| How sick do you feel today? |  |  |  |  |  |  |  |  |

Please rate the average severity of your cold symptoms over the last 24 hours for each symptom:

|                  | Do not have this symptom
0 | Very mild
1        | Mild
2             | Mild
3             | Moderate
4         | Moderate
5         | Severe
6           | Severe
7           |
|------------------|-------------------------------|-----------------------|-----------------------|-----------------------|-----------------------|-----------------------|-----------------------|-----------------------|
| Runny nose       |          |  |  |  |  |  |  |  |
| Plugged nose     |          |  |  |  |  |  |  |  |
| Sneezing         |          |  |  |  |  |  |  |  |
| Sore throat      |          |  |  |  |  |  |  |  |
| Scratchy throat  |          |  |  |  |  |  |  |  |
| Cough            |          |  |  |  |  |  |  |  |
| Hoarseness       |          |  |  |  |  |  |  |  |
| Head congestion  |          |  |  |  |  |  |  |  |
| Chest congestion |          |  |  |  |  |  |  |  |
| Feeling tired    |          |  |  |  |  |  |  |  |

Over the last 24 hours, how much has your cold interfered with your ability to:

|                              | Not at all
0       | Very mildly
1      | Mildly
2           | Mildly
3           | Moderately
4       | Moderately
5       | Severely
6         | Severely
7         |
|------------------------------|-----------------------|-----------------------|-----------------------|-----------------------|-----------------------|-----------------------|-----------------------|-----------------------|
| Think clearly                |  |  |  |  |  |  |  |  |
| Sleep well                   |  |  |  |  |  |  |  |  |
| Breathe easily               |  |  |  |  |  |  |  |  |
| Walk, climb stairs, exercise |  |  |  |  |  |  |  |  |
| Accomplish daily activities  |  |  |  |  |  |  |  |  |
| Work outside the home        |  |  |  |  |  |  |  |  |
| Work inside the home         |  |  |  |  |  |  |  |  |
| Interact with others         |  |  |  |  |  |  |  |  |
| Live your personal life      |  |  |  |  |  |  |  |  |

Compared to yesterday, I feel that my cold is ...

| Very much better      | Somewhat better       | A little better       | The same              | A little worse        | Somewhat worse        | Very much worse       |
|-----------------------|-----------------------|-----------------------|-----------------------|-----------------------|-----------------------|-----------------------|
|  |  |  |  |  |  |  |

WURSS-21® (Wisconsin Upper Respiratory Symptom Survey) 2004  
Created by Bruce Barron MD PhD et al., UW Department of Family Medicine, [name]

### 13.6.2 Common cold assessment at V2

Within 1-3 days after start of the symptoms, the subject should attend the Visit 2 at the investigational site. The subjects will be instructed (in the subject diary) to contact the site accordingly.

If the limitation of 3 days may not be held due to e.g. weekend and/or holiday, the Visit 2 could take place on the day following the last non-working day but needs to be clearly documented in the CRF record for Visit 2, together with an explanation to the delayed visit.

During Visit 2, the investigator will perform a physical examination and check the subject diaries.

In some subjects, the initial cold symptoms may possibly not further deteriorate up to a full cold outburst. During the Visit 2, the investigator has to specifically examine whether the cold symptoms initially reported by the subject in the diary are still present and whether any new additional symptoms relevant for the assessment of common cold have appeared.

For (any) observed relevant symptoms, the investigator has to judge whether they are attributable to common cold or if the subject suffers from another ailment (differential diagnosis).

The possible outcome of the investigator's assessments are:

- the subject has a common cold
- the subject suffers from another ailment (e.g. allergic rhinitis, influenza, sinusitis, pharyngitis, tonsillitis, laryngitis, reflux disease, infectious mononucleosis, pneumonia etc.), which needs to be documented as an AE

- the subject has neither a common cold nor any other ailment.

For each common cold, the intensity needs to be assessed and recorded:

- light=does not interfere with the subject's usual function
- moderate=interferes to some extent with the subject's usual function
- severe=interferes significantly with the subject's usual function.

Based on the evaluation of any relevant symptoms by the investigator at V2 (whether they are attributable to common cold), the percentage of subjects with clinically diagnosed common cold will be assessed.

### **13.6.3 Global Evaluation of Efficacy by the Subjects and Investigators**

The subjects and the investigators will evaluate independently the efficacy of the IP by means of a global scaled evaluation with "very good", "good", "moderate" and "poor" at study end.

## **13.7 ASSESSMENT OF SAFETY**

### **13.7.1 Blood Pressure and Pulse Rate**

Sitting blood pressure and pulse rate will be measured using standard products and procedures at all study visits.

### **13.7.2 Adverse Events**

Any AE that occurs during the course of the clinical investigation (for evaluation and reporting see section 14), will be recorded in the CRF. The common cold will not be documented as an AE (being the research object of the study), except in case it is an SAE.

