## 4 INTRODUCTION

A common cold is a self-limited viral infection of the upper respiratory tract (Tyrrell, 1996). Acute respiratory diseases are among the most frequent illnesses of all. They are almost exclusively caused by viruses and mostly show a natural history affecting all age groups, with well-known autumn/winter peaks (Wagner, 1996).

The typical progression differs in individuals, yet in all cases common cold presents a burden for the affected person's quality of life. Most commonly, adult subjects complain of a general feeling of sickness, nasal congestion, headache, rhinorrhea (runny nose), sore throat, hoarseness, cough and altered quality of sleep. In general, the symptoms reach maximal severity 2 to 3 days following infection, with an average overall duration of 7 to 10 days (Heikkinen & Jarvinen, 2003). A sore scratchy throat is most often a harbinger of the common cold appearing on the first day of illness; rhinorrhea and nasal congestion soon follow (Witek et al., 2015). A treatment used at the first sign of a cold that targets the scratchy upper pharynx and thereafter reduces throat and nasal symptoms, would be much desired.

Effective curative options are few due to the multiple virus types and the complex interaction between virus and host (Johnston, 1997; Hendley, 2008). Numerous symptomatic remedies are available over the counter, yet there is still no reliable treatment and their potential side effects may be substantial (Eccles et al., 2010). Effective solutions with minimal side effects (given the nonhazardous nature of the disorder) are required.

CMS008618 is ColdZyme® Mouth Spray, a marketed Class I medical device (Enzymatica AB, Sweden). It is to be used when exposed to cold viruses or early on when cold symptoms occur. It works by coating the lining of the mucous membrane, creating a protective barrier that acts osmotically on the cold viruses, trapping them and preventing them from binding with human cells, helping the body to remove them naturally.

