### **7.2 ANTICIPATED ADVERSE DEVICE EFFECTS**

The essential requirements relevant for the device safety and performance have been assessed within an extensive risk management process, which incorporates biological evaluation, design, usability, production, quality and regulatory processes and clinical validation. Evaluation of the analysis combining all potential risks has concluded that the ColdZyme® Mouth Spray is free from unacceptable risk (IB, 2018). No contraindications for use of the device, other than hypersensitivity to any of the ingredients, have been identified in the risk management process. Risks have been further addressed in post-market surveillance and in post-market investigations. No new or unacceptable risks have been recorded, and no adverse events related to the use of the ColdZyme® Mouth Spray have been reported during post-market investigations. The chosen ingredients are well known and non-toxic. Trypsin, glycerol, calcium chloride, water, ethanol and menthol are listed in the “Generally Recognized As Safe” (GRAS) substance database of the U. S. Food and Drug Administration. Therefore, the device is concluded to achieve its intended purpose and fulfil essential requirements regarding safety and performance. For further details, please refer to the IB (2018).

The study subjects will be instructed on the relevant precautions applying to CMS008618 (ColdZyme® Mouth Spray), according to the IB (2018):

- It is not to be used by individuals hypersensitive/allergic to any of the ingredients
- The user should not inhale when applying the spray since this may cause transient asthma-like symptoms, such as coughing and hoarseness

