### 8.3 OTHER SECONDARY ENDPOINTS

To be assessed in comparison between verum and placebo:

- AUC days 1-8 for each single WURSS-21 QoL subscore item
- AUC days 1-8 composite daily severity of all local symptoms within the Jackson score (mean of morning and evening)
- AUC days 1-8 composite daily severity of each individual symptom of the Jackson score (mean of morning and evening)
- Frequency of subjects with use of concomitant treatment (including natural health products) that may affect common cold symptoms - immune suppressants/immune stimulants, analgesics/anti-rheumatics, anti-phlogistics, antitussives/expectorants, mouth or throat therapeutics, decongestants, antibiotics, anti-histaminergic drugs, nasal drops/spray or any medication/treatment known to affect common cold symptoms - at any dose, during days 1-4 (based on diary data)

- Assessment of duration of first intense phase, expressed as number of days from start of treatment until scoring <5 in total Jackson score
- Assessment of symptom intensity, expressed as mean total Jackson score days 1-4
- Assessment of symptom sore throat per Sore Throat Scale, expressed as AUC days 1-8
- Percentage of subjects with confirmed common cold at Visit 2 (from all subjects with V2)
- Global evaluation of efficacy by subjects and investigators at study end

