### 11.3 DOSAGE AND USE OF IP

The IP (verum and placebo) should be applied every second hour up to 6 times per day with 2 sprays (1 dose) per dose occasion. At V1, the subject will be instructed on the use and the application demonstrated (see section 5.6).

Depending on the timepoint of treatment onset, there may be less IP applied on the first day of use.

The IP use should start when following conditions have been fulfilled:

- answering "Yes" to either of the questions in the subject daily diary: "Do you think/feel you have a cold?" or "Do you think/feel you are coming down with a cold (might be having the first signs of cold)?" AND
- A Jackson score of at least 1 in the subject's cold diary (mild = present, but not disturbing or irritating) for any symptom except headache

The IP should be used until 2 days after the subject is symptom free (=answering "No" to the question "Do you think that you are still sick with this respiratory infection?" for 2 days in a row), but not longer than 10 days in total.

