#### 15.12 ANALYSIS OF SAFETY ENDPOINTS

All subjects treated at least once with the IP will be used to evaluate issues of tolerability and safety. Safety evaluations will be based on assessment of adverse events, the global evaluation of tolerability by subject and investigator, physical examination, vital signs, and assessment of adverse device effects and reporting of device deficiencies.

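### Coughing and hoarseness are both the spray's named inhalation reaction and usual cold symptoms, and section 13.7.2 does not say how to tell them apart for AE recording

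*Protocol*

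**What the plan says.** - Section 7.2, on anticipated device effects, gives two precautions. One is hypersensitivity. The other is: "The user should not inhale when applying the spray since this may cause transient asthma-like symptoms, such as coughing and hoarseness".
- Section 4 includes among the usual adult cold complaints "rhinorrhea (runny nose), sore throat, hoarseness, cough and altered quality of sleep".
- Section 11.3 starts use of the product only once the subject reports a cold, or its first signs, with a Jackson score of at least 1 for a symptom other than headache. On stopping it says "The IP should be used until 2 days after the subject is symptom free", with a ceiling of 10 days.
- Section 13.7.2 states: "The common cold will not be documented as an AE (being the research object of the study), except in case it is an SAE".
- Section 13.6.2 has the investigator judge at V2, for the symptoms observed, "whether they are attributable to common cold or if the subject suffers from another ailment (differential diagnosis". The listed outcomes are a cold, another ailment (which is documented as an AE), or neither.
- Section 15.12 describes the safety analysis: "Safety evaluations will be based on assessment of adverse events, the global evaluation of tolerability by subject and investigator, physical examination, vital signs", together with device effects and deficiencies.
- Section 8.3 uses the diary cough score for efficacy: "AUC days 1-8 composite daily severity of each individual symptom of the Jackson score (mean of morning and evening").

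**The concern.** Apart from hypersensitivity, the reaction in 7.2 is the only device effect the protocol names, and both of its example symptoms are also cold symptoms. Every treated subject has reported a cold or its first signs, and the cold is kept out of AE documentation unless serious. A brief, non-serious cough or hoarseness set off by spraying at home can easily be put down to the cold, by the subject or later by the investigator. It then never becomes an AE, receives no judgement of relationship to the product, and does not reach the AE tables.

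At stake is what a low count would mean. If the trial reports few such reactions, the reader could not tell whether the spray seldom causes them or whether they were absorbed into the cold. No later analysis can recover events that were never collected, so the statistical analysis plan cannot repair this.

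**Working it through.** The protocol states no figure on this point, so the check sets the sections side by side.

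1. **Overlap.** Section 7.2 gives two example symptoms for inhalation, cough and hoarseness. Both are on the section 4 list of cold complaints.
2. **Exposure.** Under 11.3, use begins with the reported cold and ends two days after the subject is symptom free, or at 10 days. Nearly all exposure therefore falls while cold symptoms are present or expected.
3. **Exemption.** Section 13.7.2 exempts the cold as a disease. It does not mention single symptoms and does not refer to the reaction in 7.2.
4. **Attribution at V2.** None of the three outcomes in 13.6.2 is a reaction to the spray.
5. **General duty.** Section 14.1.1 counts device-related events as AEs, and 14.1.2 counts the results of use error as adverse device effects. Section 14.2.1 requires observed and reported AEs to be recorded with relationship to the product. A recognised reaction is covered. Relationship is assessed only once something has been called an AE, however, and 15.12 analyses reported AEs.
6. **Device-deficiency route.** Section 14.1.3 includes use error, 14.2.2 has subjects asked about deficiencies after use, and 15.12 carries deficiencies that cause an AE into the AE evaluation. This route is open too, but the question is general and does not ask about symptoms on spraying.
7. **Other safety measures.** Global tolerability (13.7.3) is a four-category rating that names no symptom. Examination and vital signs at V2 and V3 are unlikely to catch a transient reaction at home.
8. **Diary.** Cough is one of the 8 Jackson items but is planned as efficacy. Hoarseness is not a Jackson item. On the WURSS-21 form in 13.6.1 it is item 8 (one overall item, then seventh of the ten symptoms), and only items 12 to 20 are applied. One of the two named symptoms thus has a scored item, and the other has none.

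**Size.** The inputs needed are the number of verum users, the true reaction rate r, and the share c of reactions recognised and recorded. Take about 200 verum users, half of the 400 in sections 10.1 and 15.3; this is an assumption, since 15.3 itself expects the split may depart from 1:1. The protocol gives neither r nor c, so both are assumed over a range. The chance that no reaction is reported is (1 − r × c)^200. For example, r = 2% and c = 10% give (1 − 0.002)^200 = 0.998^200 = 67%.

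| r | c = 10% | c = 50% | c = 100% |
|---|---|---|---|
| 2% | 67% | 13% | 1.8% |
| 5% | 37% | 0.6% | 0.004% |
| 10% | 13% | 0.004% | below 0.0001% |

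The result runs from likely to practically impossible, depending on inputs the documents do not supply. The table shows only that the size is undetermined.

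**The case against.** The strongest reply is that the protocol already covers this reaction. The exemption names the disease, not cough or hoarseness, and the sentence before it requires any AE to be recorded. Inhaling against the precaution is plausibly a use error, so its result is an adverse device effect under 14.1.2 and may also count as a device deficiency under 14.1.3. Subjects are told of this precaution, and application is demonstrated at V1, so they know the spray can cause such symptoms. The close timing with spraying helps distinguish the reaction from a cold. Intolerance of the product is a documented withdrawal reason (13.8.1). Asthma and other airways disease are among the conditions listed for exclusion (10.4). Section 7.2 reports no related adverse events in post-market investigations, and section 6.2 gives a complaint rate of 0.014%; neither is an incidence rate, but neither suggests a frequent problem.

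Most of this stands. A reader might infer that 13.7.2 forbids reporting the reaction, or that the trial, followed as written, must report few or no cases. The documents support neither reading: a recognised spray reaction has to be recorded. What the reply does not answer is the step before recognition. No section says how symptoms on spraying are told apart from the cold, and no question is directed at them. Training may make the reaction rarer or easier to recognise, but it does not ensure that it is asked about.

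**Conclusion.** The point holds as a weakness in how safety events are ascertained, not as an error of analysis and not as a ban on reporting. The device's own named reaction consists of symptoms the protocol also assigns to the cold, arises almost only while a cold is being reported, and has neither an attribution rule nor a targeted question. Hoarseness also lacks a scored diary item.

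That some reactions will be misattributed is a judgement about how subjects and investigators behave; the text permits it but does not establish how often. The extent of under-reporting cannot be stated from the documents, and no single figure should be quoted for it. The primary analysis and the sample size are untouched. Given a transient, non-serious effect of a marketed Class I device, this is an inexpensive improvement worth making rather than a fault that threatens the trial.

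**What to change.** 1. In 13.7.2, state that the exemption for the cold does not extend to cough, hoarseness or other asthma-like symptoms that begin or worsen on or directly after spraying, and that these are documented as AEs with a causality assessment.
2. Add one blinded prompt on such symptoms, worded the same in both arms, to the AE and device-deficiency questioning already scheduled at V2 and V3.
3. Report these events by arm within the AE tables already planned in 15.12.

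A separate safety table of new cough from the Jackson score should not be added. Cough often develops as a cold progresses, and any efficacy on cough would pull the comparison the other way, so the table could not isolate a spray reaction.

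The cost is one sentence, one prompt and a few rows in existing tables, with no new visit or procedure. The downside is that a few more non-serious AEs will be recorded, so tolerability may look slightly less favourable.
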